**Study Analysis Methods**

**Aim 1 Analysis.** Our Aim 1 hypothesis is:

Hypothesis 1.1: *We will successfully engage key stakeholders in a community-based participatory research approach to develop the content and structure of the RGT program to accommodate current clinical practice guidelines and integrate emerging robotic exoskeleton technology.*

The Advisory Board of key stakeholders (patients, caregivers, clinicians, researchers, industry members) to review evidence-based literature, advise the research team on the unique aspects and goals of inpatient rehabilitation for people with SCI, review the RGT, and make recommendations for amendments to the RGT program based on our interim and final outcomes of the study over the funding period. The role of the advisory board is necessary to meet the needs of individuals post SCI based on previously demonstrated successful inclusion of RGT into clinical practice during inpatient rehabilitation and detected change in key outcome variables.

**Aim 2 Analysis.** Our Aim 2 hypotheses were:

*Hypothesis 2.1:* *Patients with incomplete SCI who receive RGT will have higher walking function (WISCI-II) at discharge compared to UC.*

*Hypothesis 2.2: Patients with incomplete SCI who receive RGT will have greater improvement of secondary outcomes (gait speed, daily function independence, pain, fatigue, spasm frequency, depressive symptoms, and quality of life) at discharge compared to UC.*

All analysis will be performed using SAS 9.4 with a significance level of 0.05. To determine if patients with incomplete SCI who receive RGT will have higher walking function than UC at discharge (Hypothesis 2.1), WISCI-II scores will be evaluated using a linear model. The distribution of WISCI-II scores will be assessed to determine if a general linear model will be utilized, or if a generalized linear model with an alternative distribution and link function, such as the gamma distribution with a log link, will be more appropriate. Similarly, all measures associated with the secondary outcomes in Hypothesis 2.2 (10MWT, SCIM, NPRS, FSS, PSFS, PHQ-9, LiSAT-9) will be evaluated with general or generalized linear models, as appropriate. A separate model will be run for each outcome. All models for both the primary and secondary outcomes will control for scores at admission as well as the patient’s demographic and impairment information listed in section B.1.i.D.

**Aim 3 Analysis:** Our Aim 3 hypotheses were:

Hypothesis 3.1: *RGT will be of significantly greater intensity with participants (1) spending more minutes per session and total minutes (over all sessions) in moderate intensity exercise (40% to 60% range of heart rate reserve), (2) reporting higher mean RPE across all sessions, and (3) completing more steps during each session and total number of steps over all sessions compared to UC.*

Hypothesis 3.2: *Intensity will be significantly correlated to the primary outcome (WISCI-II) for the RGT and UC groups.*

Hypothesis 3.1 will be evaluated using similar methods as Aim 2. Moderate intensity minutes, average RPE, and steps will be evaluated using individual general or generalized linear models, as appropriate, to determine the association between RGT and UC and intensity. Each model will control for the patient characteristics listed in section B.1.i.D and total number of sessions. Additionally, to determine the relationship between session intensity and walking function (Hypothesis 3.2) correlation coefficients will be calculated between each intensity measure and WISCI-II at admission, discharge, and change score.

For both Aims 2 and 3 stratified subset analysis will be performed for tetraplegia and paraplegia to determine if RGT has a differing impact depending on injury classification.

**Missing Data:** If a patient misses an assessment, their data for that outcome will be treated as missing and *will not* be included in the statistical model. However, the data from the completed assessments for that patient *will* be included. Sensitivity analysis will be performed to assess the impact of missing data, by imputing a missing outcome measure using the overall average change score for the given outcome. The sensitivity analyses will be compared to the initial analysis to determine the impact of missingness on the results

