Progression of the RGT intervention will be individualized to accommodate injury severity characteristics and variable rates of functional recovery. However, a general approach to progression of RGT will include the following sequential steps: (1) familiarization with Ekso stepping and weight shift pattern, (2) standing tasks > walking tasks, (3) walking tasks > standing tasks, (4) program reduced maximal assistance provided by Ekso during walking, (5) program zero assistance provided by Ekso during walking, (6) program resistance provided by Ekso during walking. This progression is based on recommendations during Ekso training and our therapists’ clinical experience.^81,82^

All RGT activities will be conducted with the necessary supervision and assistance from a licensed physical therapist trained in the use of Ekso robotic exoskeleton.

BSW owns 2 Ekso robotic exoskeleton devices for research purposes that will be used in this study. Extended service contracts will be purchased to ensure the continual maintenance of the Ekso devices for the duration of the study. Ten physical therapists have been trained to use the Ekso for mobility and gait training, successfully completing Level I (basic) and Level II (advanced) training under the supervision of an Ekso trainer. The therapists have an average of nearly 2-years’ experience conducting RGT and 7.5 years of inpatient rehabilitation experience working with patients with SCI.

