**Visit Windows**

Patients will be asked to complete testing at 2 time points: within one week of admission to inpatient rehabilitation and within one week of discharge from inpatient rehabilitation.

| **Table 6: Patient Timeline** | | | | |
| --- | --- | --- | --- | --- |
| Study Phase | Admission | Treatment (UC or RGT) Intervention | Discharge | Data Source |
| **Consent** | X |  |  |  |
| Demographics | X |  | X | Medical Record |
| **Outcome Testing** |  |  |  |  |
| *Aim 2* |  |  |  |  |
| Walking Score Index for Spinal Cord Injury (WISCI-II) | X |  | X | Medical Record |
| 10-meter walk test (10MWT) | X |  | X | Medical Record |
| Spinal Cord Independence Measure (SCIM) | X |  | X | Medical Record |
| Numeric Pain Rating Scale (NPRS) | X |  | X | Medical Record |
| Fatigue Severity Scale (FSS) | X |  | X | Study Specific |
| Penn Spasm Frequency Scale (PSFS) | X |  | X | Study Specific |
| Patient Health Questionnaire – 9 (PHQ-9) | X |  | X | Study Specific |
| General Anxiety Disorder – 7 (GAD – 7)  International SCI Quality of Life Basic Data Set  Qualitative Questionnaire | X  X |  | X  X  X | Study Specific  Study Specific  Study Specific |
| *Aim 3* |  |  |  |  |
| Heart Rate (HR) |  | X |  | Study Specific |
| Ratings of Perceived Exertion (RPE) |  | X |  | Study Specific |
| Number of steps |  | X |  | Study Specific |

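### The Hypothesis 3.1 intensity models adjust for no baseline walking measure; adding admission WISCI-II would be a nearly free, optional gain in precision, most plausibly for step counts

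*Protocol*

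**What the plan says.** Protocol section 9, Study Analysis Methods, treats the two aims differently.

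- **Aim 2:** "All models for both the primary and secondary outcomes will control for scores at admission as well as the patient’s demographic and impairment information", the latter as listed in section B.1.i.D. Admission scores are thus named separately from the B.1.i.D characteristics.
- **Aim 3, general method:** "Hypothesis 3.1 will be evaluated using similar methods as Aim 2".
- **Aim 3, outcomes:** "Moderate intensity minutes, average RPE, and steps will be evaluated using individual general or generalized linear models", as appropriate.
- **Aim 3, covariates:** "Each model will control for the patient characteristics listed in section B.1.i.D and total number of sessions".

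Table 6 schedules WISCI-II at admission and discharge, with testing "within one week of admission to inpatient rehabilitation and within one week of discharge from inpatient rehabilitation". Heart rate, RPE and steps are recorded only during treatment. Hypothesis 3.2 expects intensity to correlate with WISCI-II in both groups, and the plan calculates correlations with the admission, discharge and change scores. Randomisation (section 5) is 1:1, stratified by tetraplegia or paraplegia only.

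**The concern.** The Aim 3 sentence keeps the B.1.i.D characteristics, adds the session count and names no admission score. The general reference to Aim 2 methods does not fill the gap. The intensity measures have no admission value of their own, so there is nothing to carry over unless a walking baseline is named.

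How many steps a patient takes plausibly depends on how well that patient walks on entry. The protocol itself says: "Progression of the RGT intervention will be individualized to accommodate injury severity characteristics and variable rates of functional recovery". It also expects sessions to shift from standing towards walking as training proceeds. Eligibility is broad (traumatic and non-traumatic incomplete injury, ages 16 to 85, within 6 months), and section 5 calls the spread of severity a concern.

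Two things are at stake. Outcome variance that admission walking ability would explain stays in the error term. And a chance difference between arms in admission walking ability is only partly taken up by the strata and the severity covariates. Hypothesis 3.1 is a formal superiority claim, so lost power matters to it. The Hypothesis 3.2 correlations are not affected.

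**Working it through.** **Inputs from the protocol (section 9, Sample Size Considerations):** 64 per group, effect size 0.5, 80% power, 5% significance, about 10% attrition. Sidedness is not stated; two-sided reproduces the sample size.

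**Input not in the protocol:** r, the correlation of admission WISCI-II with an intensity outcome after the covariates already in the model. I take 0 to 0.7 as an assumed range.

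**Step 1, the plan's own figure.** Normal approximation: n per arm = 2 × (1.960 + 0.842)² / 0.5² = 62.8, so 63. The exact two-sample t-test gives 63.8, so 64, with power 80.1% at 64 per arm. The stated 64 is reproduced, before any attrition.

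**Step 2, adding the covariate.** A baseline covariate with partial correlation r multiplies the residual SD by √(1 − r²), so the effective standardised difference is 0.5 / √(1 − r²). Here 0.5 is read in units of the residual SD of the model as now written. Power is from the two-sided t-test, with 64 per arm and with 57.6 per arm (64 × 0.9, for 10% loss).

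| r | Variance removed (r²) | Effective difference | Power, 64 per arm | Power, 57.6 per arm |
|---|---|---|---|---|
| 0 | 0% | 0.500 | 80.1% | 75.8% |
| 0.2 | 4% | 0.510 | 81.7% | 77.5% |
| 0.3 | 9% | 0.524 | 83.7% | 79.6% |
| 0.4 | 16% | 0.546 | 86.5% | 82.7% |
| 0.5 | 25% | 0.577 | 90.0% | 86.7% |
| 0.6 | 36% | 0.625 | 93.9% | 91.4% |
| 0.7 | 49% | 0.700 | 97.6% | 96.1% |

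At 64 per arm the gain is 1.6 points at r = 0.2, 3.6 at 0.3, 6.4 at 0.4 and 9.9 at 0.5. The difference detectable with 80% power (normal approximation) falls from 0.495 SD at r = 0 to 0.472 at 0.3 and 0.429 at 0.5.

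**Step 3, chance imbalance.** The standard error of the standardised difference in admission WISCI-II is √(2/64) = 0.177 SD. At r = 0.5, an imbalance of one standard error moves the intensity contrast by 0.5 × 0.177 = 0.09 SD. An imbalance of 1.96 standard errors moves it by 0.5 × 1.96 × 0.177 = 0.17 SD, about a third of 0.5. These are upper illustrations, since the strata and severity covariates take up part of any imbalance.

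**Limits of the arithmetic.** The t-test stands in for a general or generalized linear model with several covariates. If a gamma model with log link is chosen, the formula in Step 2 is only a guide.

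**The case against.** The case against is substantial.

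- **Nothing is invalid.** The arms are randomised, so leaving out a baseline covariate does not bias the comparison, and the standard error already allows for chance imbalance. This stands.
- **The contrast with Aim 2 is limited.** "All models for both the primary and secondary outcomes will control for scores at admission as well as" the B.1.i.D information reads most naturally as each outcome's own baseline. The secondary Aim 2 models then contain no admission WISCI-II either. A reader might infer that the protocol contradicts itself; it does not. The parallel holds only with the primary model for Hypothesis 2.1.
- **Severity may already carry much of the information.** Section 6 lists injury severity and AIS among the collected characteristics, and section 9 says B.1.i.D contains impairment information. No section of that number appears in this protocol, so what is left for WISCI-II to explain cannot be judged.
- **The mechanism is uneven.** A reader might infer that entry walking ability limits all three measures. Moderate-intensity minutes are defined by the patient's own heart rate reserve, RPE is self-rated exertion, and RGT steps are taken with powered assistance. The link is clear mainly for steps, and best for steps in usual care.
- **The effect size is borrowed.** The 0.5 is a generic medium effect, not an Aim 3 assumption. The background reports about 66% against 42% of time in moderate intensity, without an SD. If the true standardised difference is large, power is already high and the gain is small.

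These points limit the size and reach of the concern but do not remove it. The covariate list is fixed in the protocol, it contains no walking baseline, and Hypothesis 3.2 shows that the investigators themselves expect WISCI-II and intensity to be related in both groups.

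**Conclusion.** The point holds as a free improvement: an optional gain in precision for a supporting aim. The Hypothesis 3.1 models omit a baseline that is already scheduled for everyone and that the protocol gives reason to think prognostic.

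The size is conditional. Under a 0.5 SD difference and 64 per group, the gain is under 2 points of power for r of 0.2 or less, about 4 points at 0.3 and about 10 at 0.5. It needs r of about 0.4 to exceed 5 points. Here r counts only what WISCI-II adds beyond severity and AIS, so the true gain may lie at the low end. It is most plausible for step counts, especially in usual care, and may be small for RPE and heart-rate-reserve minutes.

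A reader might infer that the intensity comparison is biased, or that imbalance in walking ability passes into it in full. The documents support neither: allocation is randomised and stratified, and severity is among the collected characteristics. No conclusion on the primary outcome is affected.

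**What to change.** In the Aim 3 Analysis sentence of section 9 that lists the covariates, add admission WISCI-II as a pre-specified covariate in the Hypothesis 3.1 models, as in the primary Hypothesis 2.1 model. If the sponsor prefers to limit the change, steps matter most.

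The cost is one phrase and one degree of freedom per model, with no new data. Fixing it in advance also avoids deciding on the covariate after the planned correlations with admission WISCI-II have been seen.

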UC gait training at BSWIR adheres to the current SCI-specific clinical practice rehabilitation guidelines. These guidelines recommend that body weight–supported treadmill training (BWSTT) as an option for ambulation training in addition to conventional overground walking, dependent on resource availability, context, and local expertise.^65^ BSWIR currently offers 2 BSWTT systems, 1 overground body weight-supported overground system, and various assistive devices (e.g., walkers, leg braces) to perform manually assisted overground gait training. BSW therapists are trained and proficient in providing UC gait training interventions to patients with SCI. Patients in the UC group will receive 90 minutes per week of UC gait training (e.g., BWSTT, overground with braces).

If participants are randomized into the usual care group and have completed care, they will be offered up to eight optional sessions of robotic walking training in outpatient therapy at BSWIR in Dallas, Texas. Participants will need to obtain a physician referral and arrange their own transportation.

*RGT*

Patients in the RGT group will receive 90 minutes per week of RGT in the Ekso device once patients are deemed clinically appropriate as defined by being able to tolerate standing for 15 minutes without orthostatic intolerance. The Ekso Bionics Ekso GT™ robotic exoskeleton will be used for RGT.

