The EksoGT™ robotic exoskeleton is a class II medical device (United States FDA) that allows patients with SCI to experience over-ground weight bearing stepping.^94^ The Ekso is a battery powered wearable bionic suit with motors at the hips and knees which enables individuals with lower extremity motor impairment to stand and voluntarily step over-ground with weight-bearing and alternating stepping (see Figure 2). The Ekso device works in two modes namely the “max assist” and “variable assist.” In max assist, the pilot (patient) initiates a step by unweighting one leg which triggers the motors on the Ekso to move the entire limb in a step like trajectory. In this mode, 100% assistance is offered during the entire step cycle. The variable assist mode actively allows the subject to voluntarily assist, even when the subject exerts minimal voluntary influence on the robot. While stepping with the variable assistance mode, once the subject initiates a step, the Ekso only provides assistance during the swing phase based on the amount of effort the patient applies. An essential advantage of overground robotic exoskeleton devices (e.g., Ekso, Indego) over treadmill-based exoskeletons (e.g., Lokomat) is the ability to voluntarily engage the lower limbs while stepping, by engaging both supraspinal and spinal networks in a synergistic manner (*critical ingredient #1, pg 2*). This “assist as needed” paradigm allows the subject to engage the lumbosacral spinal networks to control one limb at a time to complete a swing phase while the contralateral limb goes through a passive stance phase.^94^ In the proposed study, the variable assist mode will be used exclusively. We elected to use the Ekso exclusively in this ‘intervention development’ study because the FDA indications for use accommodate a broader range of injury levels of SCI compared to other FDA approved overground robotic exoskeleton devices.

During the first RGT session, the patient will be fitted for the Ekso device. RGT will be initiated immediately thereafter. While each training session may vary in length due to medical acuity and patient tolerance, RGT will total 90 minutes/week. Based on our retrospective data, we anticipate the specific tasks during RGT to vary between standing tasks and walking, with more steps and time spent walking as the RGT sessions progress. Notably, the RGT records data for each training session including frequency, time standing, time walking, and number of steps.

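### Aim 3 adjusts total minutes and total steps for the number of sessions, a post-randomisation factor of those totals, so the totals in Hypothesis 3.1 are not tested as worded

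*Protocol*

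**What the plan says.** Hypothesis 3.1 makes separate claims per session and in total. For exercise minutes it speaks of "spending more minutes per session and total minutes (over all sessions) in moderate intensity exercise", and for steps of "completing more steps during each session and total number of steps over all sessions compared to UC". The analysis paragraph that follows (Protocol section 9, Aim 3 Analysis) gives one covariate rule for all of these outcomes: "Each model will control for the patient characteristics listed in section B.1.i.D and total number of sessions".

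Two statements in section 4, Study Treatment, bear on whether session counts can differ by arm. RGT begins "once patients are deemed clinically appropriate as defined by being able to tolerate standing for 15 minutes without orthostatic intolerance", and no such condition is stated for UC. For RGT, "each training session may vary in length due to medical acuity and patient tolerance, RGT will total 90 minutes/week", so at fixed weekly minutes the session length determines the session count.

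Hypothesis 3.2 reads: "Intensity will be significantly correlated to the primary outcome (WISCI-II) for the RGT and UC groups". The only analysis named for it is that "correlation coefficients will be calculated between each intensity measure and WISCI-II at admission, discharge, and change score". By contrast, for Aim 2 "All models for both the primary and secondary outcomes will control for scores at admission".

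**The concern.** A patient's total is the number of sessions multiplied by the average amount per session. An arm can reach a higher total through more sessions, more per session, or both. The total is worth claiming separately from the per-session amount only because it includes the first route. A model that holds the session count fixed closes that route, although the count is itself a possible consequence of the assigned arm.

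The trial could therefore report that RGT delivers more total exercise when the totals are the same or lower, or miss a real difference that comes from additional sessions.

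On Hypothesis 3.2, patients who walk better at admission are likely both to take more steps in training and to score higher at discharge. A simple correlation would then appear even if intensity contributed nothing. This matters because the Rationale for Protocol in section 2 looks ahead to using the data for dose-response evaluation.

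**Working it through.** The protocol gives no figure to reproduce here, so the check is algebra and simulation. All session counts, minutes, steps and correlations below are assumptions. From the protocol come the 64 per arm, the roughly 10% attrition (64 × 0.9 = 57.6, taken as 58) and the 5% significance level, used two-sided.

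**1. Can session counts differ at equal weekly minutes?** Both arms are prescribed 90 minutes a week. Table 1 shows 30-minute sessions (90/30 = 3 a week); Table 3 allows RGT sessions up to 45 minutes (90/45 = 2 a week). Over a 22-day stay, the stated non-traumatic average, that is 22/7 × 3 = 9.4 sessions against 22/7 × 2 = 6.3. A delayed RGT start would lower the count further. This shows that gaps of one to three sessions are possible; it does not predict them.

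**2. Total minutes, true totals equal.** Poisson sessions, minutes per session with SD 6, total regressed on arm with and without the session count, 58 per arm. As a rough guide, the adjusted arm effect is close to the per-session difference multiplied by the mean session count.

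| RGT vs UC | True difference in total | Without session covariate | With session covariate | Rough guide |
|---|---|---|---|---|
| 9 × 17.8 vs 10 × 16 min | 0 | about 0 min, 5% significant | about +17 min, 31% significant | 1.8 × 9.5 = 17 |
| 8 × 20 vs 10 × 16 min | 0 | about 0 min, 5% significant | about +35 min, 88% significant | 4 × 9 = 36 |
| 10 × 19 vs 10 × 16 min | +30 | unbiased, power 46% | unbiased, power 71% | 3 × 10 = 30 |

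**3. Total steps, showing the other distortions.** 64 per arm; UC 12 sessions (SD 4) at 300 steps per session (SD 100), so 3,600 steps.

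- Hidden: RGT 15 × 300 = 4,500, true difference +900. Estimated about +897 without the covariate, about -2 with it.
- Created: RGT 9 × 400 = 3,600, true difference 0. About +9 without, about +1,044 with.
- Reversed: RGT 9 × 360 = 3,240, true difference -360. About -353 without, about +621 with.
- Harmless: RGT 12 × 360 = 4,320, true difference +720. About +720 without and +714 with, and power rises from 59% to 88%.

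The adjusted model is only roughly a per-session contrast. If a patient factor drives both session count and steps per session (assumed loadings 0.5, in opposite directions), then with no true per-session difference it gives about +254 steps when RGT has three more sessions and about -202 when it has three fewer.

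**4. Hypothesis 3.2.** Suppose intensity correlates 0.6 with admission WISCI-II, admission correlates 0.7 with discharge, and intensity has no further effect.

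- Intensity with discharge: 0.6 × 0.7 = 0.42, significant in 91% of trials at 57 per arm and 94% at 64 (Fisher z).
- With 0.4 and 0.6 instead: 0.24, significant in 44% to 48%.
- Intensity with change, equal SDs: (0.42 - 0.60)/√(2 - 2 × 0.7) = -0.18/0.775 = -0.23.
- Partial correlation given admission: 0 in both cases.

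**The case against.** The session covariate has a sensible purpose. Section 4, Recruitment, reports average stays of 35 days for traumatic and 22 days for non-traumatic injury, varying with insurance approval and medical complexity. Much of the variation in sessions is therefore unrelated to arm, and adjusting for it removes noise. The prescribed weekly dose is the same in both arms, and late consent is allowed for patients not yet medically suitable, so part of any delay may fall before randomisation. All of this stands. It supports a session-adjusted model as a supplement, not as the only test of a claim about totals.

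A reader might infer that the comparison of totals will certainly be biased. The documents do not support that: they give no session counts by arm, and with equal counts there is no bias. The per-session outcomes and mean RPE lie outside this point.

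A reader might also infer that Hypothesis 3.2 goes unanswered. It does not: the hypothesis claims only a correlation, and the planned coefficients supply one. Nor is admission ability ignored. The admission correlation would show the baseline link, and in the scenario above the change score would correlate negatively, which does not look like a training benefit. Change scores do not remove the confounding, but the plan's own output would hint at it.

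Finally, one could count 30 tests (five intensity measures × three WISCI-II versions × two arms). The analysis sentence names three measures, which gives 18. Multiplicity in a descriptive aim, and the choice of a lead measure, are matters a statistical analysis plan commonly settles.

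**Conclusion.** The point on totals holds. The protocol states total minutes and total steps as claims of their own, then fixes a model that conditions on one of the two factors of each total, and that factor arises after randomisation. As written, the total part of Hypothesis 3.1 is not estimated.

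The size of the harm is conditional. In the assumed equal-totals scenarios, a gap of one session gives a false difference of about 17 minutes on 160 and a gap of two gives about 35; a gap of zero gives none. The protocol provides mechanisms for a gap but no evidence of one. This is a secondary aim, and the primary WISCI-II analysis is untouched.

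On Hypothesis 3.2 the conclusion is a limit on interpretation: the simple correlations meet its wording, but they cannot carry a dose-response reading, because a correlation of 0.42 can arise from admission ability alone under the assumed inputs.

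**What to change.** In Aim 3 Analysis, restrict the session covariate so that it does not enter the primary models for total moderate-intensity minutes and total steps. Report the number of sessions per arm beside them. If a session-adjusted model of the totals is wanted, keep it as supportive and label it a per-session contrast.

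For Hypothesis 3.2, keep the planned correlations, including the one with admission WISCI-II as a diagnostic, and add a within-arm correlation of intensity with discharge WISCI-II adjusted for admission WISCI-II. Refer to that one in any dose-response statement.

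The cost is a few sentences of wording; the variables are already collected. The statistical price is precision for the totals when session counts are in fact equal: in the assumed case of 19 versus 16 minutes per session, power is 46% instead of 71%.

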Hypothesis 3.1: *RGT will be of significantly greater intensity with participants (1) spending more minutes per session and total minutes (over all sessions) in moderate intensity exercise (40% to 60% range of heart rate reserve), (2) reporting higher mean RPE across all sessions, and (3) completing more steps during each session and total number of steps over all sessions compared to UC.* Our hypothesis is based on the theoretical rationale described in **Tables 3** and **Table 4** below, our previous work,^12^ and will incorporate input from the Advisory Board regarding these variables and adjust the intensity as suitable.

Hypothesis 3.2: *Intensity will be significantly correlated to the primary outcome (WISCI-II) for the RGT and UC groups.*

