# **9 STATISTICAL METHODS**

**Sample Size Considerations**

For the proposed project, 128 patients (64 per group) will be enrolled. All analysis will be performed using SAS 9.4 significance set at the 5% level. Sample size calculations were performed to determine the required sample size in each group based on detectable effect size. For 80% power with a 5% significance level we will need to obtain 64 participants in each group to detect a medium effect size of 0.5 and allow for ~10% attrition due to unplanned medical events, acute care transfers, and patient withdrawals. We anticipate minimal attrition as all treatments and outcomes will be assessed during the inpatient rehabilitation stay and we experienced 0% attrition during our feasibility study.

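### Hypothesis 3.2 is tested by a grid of unadjusted correlations with no deciding cell, including one with baseline WISCI-II, so a significant result may show only that better walkers train harder

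*Protocol*

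**What the plan says.** Section 3 (Study Aims) and section 9 (Aim 3 Analysis) both state Hypothesis 3.2 as a claim of significance: "Intensity will be significantly correlated to the primary outcome (WISCI-II) for the RGT and UC groups".

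Section 9 gives the analysis: "correlation coefficients will be calculated between each intensity measure and WISCI-II at admission, discharge, and change score". The significance level is stated twice, under Sample Size Considerations ("All analysis will be performed using SAS 9.4 significance set at the 5% level") and under Study Analysis Methods ("All analysis will be performed using SAS 9.4 with a significance level of 0.05").

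The number of intensity measures depends on which sentence is read. The analysis text for Hypothesis 3.1 lists three: "Moderate intensity minutes, average RPE, and steps will be evaluated using individual general or generalized linear models". The hypothesis itself splits two of these into per-session and total versions: "spending more minutes per session and total minutes (over all sessions) in moderate intensity exercise" and "completing more steps during each session and total number of steps over all sessions compared to UC". With mean RPE that makes five.

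For Hypothesis 3.2 the protocol names no deciding measure and no deciding WISCI-II version. It does not say whether one group or both must show the correlation, and it plans no adjustment for the admission score. The Aim 2 models, by contrast, do control for admission scores.

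**The concern.** Three quantities that answer different questions stand on equal terms as tests of one hypothesis.

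- **Admission WISCI-II** is the baseline. Table 6 places it before the treatment phase. A correlation with it describes who trains hard, not what training does.
- **Discharge WISCI-II** carries baseline ability forward, so it inherits that relationship.
- **The change score** subtracts the baseline and can inherit the relationship with the opposite sign.

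Confounding of this kind is to be expected here. Section 4 says that RGT is progressed individually according to injury severity and rate of recovery, and Table 2 ties its intensity to what each patient tolerates. Patients who walk better at admission will plausibly take more steps.

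At stake is the link between dose and outcome. Section 4 says the project will relate RGT dose to gait and function, and section 2 hopes to provide groundwork for studying dose-response. As written, a baseline-ability correlation, or the best of many cells, could be reported as support for Hypothesis 3.2.

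**Working it through.** **Inputs from the protocol.** Significance level 0.05 (taken as two-sided); "128 patients (64 per group) will be enrolled"; three or five intensity measures; three WISCI-II versions; two groups.

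**Assumptions, because the protocol gives no figures.** Correlation among intensity measures 0 to 0.8; admission-discharge WISCI-II correlation 0.3 to 0.8 (it hardly matters in step 3); all 64 per group analysed; Pearson tests on normal data.

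**1. The plan's own figure.** The protocol states no error rate for Hypothesis 3.2. Its only related figure, 64 per group for an effect size of 0.5 at 80% power, reproduces with a two-sample t-test (63.8, rounded up to 64). With n = 64 a correlation is significant when |r| > t/√(62 + t²) = 1.999/√(62 + 3.996) = 0.246.

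**2. Number of tests.** 3 × 3 × 2 = 18, or 5 × 3 × 2 = 30. If the tests were independent, the chance of at least one false positive would be 1 − 0.95^18 = 60.3% or 1 − 0.95^30 = 78.5%. They are not independent, so these are only ceilings.

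**3. False positives when intensity is unrelated to WISCI-II (simulation).**

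| Measures | Correlation among measures | A hit in either group | A hit in each group |
|---|---|---|---|
| 3 | 0.8 | 39–41% | 5% |
| 3 | 0.5 | 48–49% | 8% |
| 3 | 0 | 54–55% | 10% |
| 5 | 0.8 | 48–49% | 8% |
| 5 | 0.5 | 62–65% | 16–17% |
| 5 | 0 | 72–74% | 21–24% |

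The last two columns are linked. If one group has chance p, the two rules give 1 − (1 − p)² and p². With five measures at 0.5, p is about 0.39, giving 1 − 0.61² = 63% and 0.39² = 15%.

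Other readings, at correlation 0.5 among measures unless a range is given:
- one pooled group of 128: 29% (three measures) or 41% (five);
- discharge only, a hit in either group: 20% to 26% for three measures (correlation 0.7 to 0), or 33% for five.

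**4. Confounding by baseline ability.** Let intensity correlate r with admission WISCI-II, let admission and discharge correlate 0.7 with equal variances, and let intensity have no link to recovery. The implied correlations are:
- discharge: 0.7r;
- change: (0.7r − r)/√(2 − 2 × 0.7) = −0.3r/0.775.

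For r = 0.3 these are 0.30 (admission), 0.21 (discharge) and −0.116 (change). By Fisher's z, atanh(correlation) × √61 gives 2.42, 1.66 and −0.91, so the tests reject in about 68%, 38% and 15% of groups. Simulation gives about 68%, 39% and 14% to 15%. The same formula over a range of r:

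| r | Admission | Discharge | Change |
|---|---|---|---|
| 0.2 | 35% | 20% | 9% |
| 0.3 | 68% | 38% | 15% |
| 0.4 | 91% | 61% | 23% |

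The discharge and change cells also point in opposite directions.

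**5. The adjusted analysis under the same assumptions.** The partial correlation of intensity with discharge given admission has numerator 0.21 − 0.3 × 0.7 = 0. Its test rejects in 5% of groups by simulation.

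**The case against.** Several points on the other side are sound.

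- **The decision rule is not in the protocol.** A reader might infer that about half to two thirds of such trials (48% to 63%) would falsely confirm Hypothesis 3.2. The documents do not support this as a flat statement. It needs one significant cell in either group to count as confirmation, and an assumed correlation of 0.5 among the measures. The hypothesis speaks of the RGT and UC groups together and can as naturally be read as requiring both, which lowers the figure to about 5% to 24%. The upper end also needs five measures, where the Aim 3 analysis text lists three.
- **There is a hint at discharge.** Hypothesis 3.2 calls WISCI-II the primary outcome, and Hypothesis 2.1 places that outcome at discharge. So it would be too strong to say that nothing points to a version. But the analysis sentence then lists all three versions without distinction.
- **The admission correlation has a proper use.** It is a reasonable check on baseline confounding, and listing it need not mean that it is offered as proof of effect. The protocol does not give it that role, though.
- **Some of this is ordinary SAP content.** A SAP that is not shown may name the deciding contrast. That covers an omission. It does not cover an analysis that the protocol itself writes out and that, followed literally, counts a baseline score toward a significance claim and leaves the other two versions unadjusted.
- **The stakes are limited.** Table 7 describes Aim 3 as descriptive, and dose-response appears only as a long-term hope. This bears on severity, but the hypothesis is still worded as a test of significance.

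Making the change score the deciding quantity would not answer the concern: it still rejects in about 14% to 15% of groups in step 4.

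**Conclusion.** The concern holds in this form. The analysis of Hypothesis 3.2 has no deciding cell, gives a baseline score equal standing, and leaves the discharge and change correlations open to confounding by baseline ability.

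The confounding needs no view on multiplicity. Under the stated assumptions (0.3 with admission, 0.7 between admission and discharge, no link to recovery, 64 per group) the rejection rates are about 68%, 39% and 14% to 15%, against a nominal 5%. The multiplicity figure depends on the rule and the assumptions: about 39% to 73% if any cell in either group suffices, about 5% to 24% if each group needs a hit. The tetraplegia and paraplegia subset analyses planned for Aim 3 are not counted and would add tests.

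The primary comparison under Aim 2 and its sample size are untouched. This is a minor-to-moderate point.

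**What to change.** In section 9, Aim 3 Analysis:

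1. Name one intensity measure for Hypothesis 3.2. Steps per session would fit section 2, which identifies step counts as the recommended way to track intensity.
2. Make the deciding analysis its association with discharge WISCI-II adjusted for admission WISCI-II, by partial correlation or regression, reported in each group with a 95% confidence interval.
3. State whether both groups must be significant. If either suffices, apply Holm across the two groups; two independent 5% tests would otherwise give 1 − 0.95² = 9.75%.
4. State that correlations with admission WISCI-II are a descriptive check for baseline confounding and cannot support the hypothesis.
5. Label all other correlations exploratory and report them as estimates with confidence intervals.

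The cost is a few sentences in section 9, carried into the SAP. No new data are needed, since the admission score is already collected, and every planned coefficient can still be reported. The downside is that only one intensity measure can be called confirmatory.
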